Platelet counts (PCs) are frequently altered in patients with sepsis, and are implicated in the pathogenesis of multi-organ failure. Thrombocytopenia is common in sepsis patients, the incidence of which is even as high as 55% [11]. There exist the following mechanisms about sepsis-related thrombocytopenia [12, 13]:1) Some toxins and inflammatory mediators induced by sepsis can inhibit the formation and release of megakaryocytes in bone marrow to cause thrombocytopenia; 2) Some toxins and inflammatory mediators induced by sepsis can directly destroy platelets; 3) Sepsis is often accompanied with local microthrombosis or even cause disseminated intravascular coagulation (DIC) to result in massive platelet depletion; 4) Thrombocytopenia can be induced by some clinical treatments for sepsis patients such as renal replace therapy (RRT), heparin and antibiotics. Until now, it has been confirmed that platelets have various biological functions, not only in hemostasis and thrombosis but also in the host defense, inflammatory/immune responses, tissue repair and regeneration [14–16]. Clinically, thrombocytopenia was closely associated with multiply organ dysfunction and the higher mortality in sepsis patients [17, 18]. Moreover, a multicenter prospective trial in France pointed out that thrombocytopenia was an early prognostic indicator for sepsis patients, and the occurrence and duration of thrombocytopenia were closely related to length of ICU stay, hospitalization stay and 28-day mortality. Furthermore, the greater the extent of thrombocytopenia was, the higher the mortality was [19]. Another study found that severe thrombocytopenia released more inflammatory factors, stimulated endothelial cells, inhibited leukocyte adhesion/activation related signaling pathways, activated complement related signaling pathways, and caused dysregulated host defense responses. Furthermore, 30-day mortality of sepsis patients with severe thrombocytopenia was more than 50% [20]. In our previous meta-analysis study, we also found that thrombocytopenia was associated with poor prognosis and increased the complication including shock, bleeding and acute kidney injury in sepsis patients [21]. Besides, the patients who had sustained thrombocytopenia or a drop-in PCs of > 30% during ICU had the higher mortality [22]. The longer the duration of thrombocytopenia is, the worse the prognosis of these patients have, and rapid recovery of PCs may reduce the mortality of these patients. In our single-center, retrospective cohort study, we found that sepsis patients with severe thrombocytopenia might have the more blood product transfusion, the shorter days free from organ support, the shorter survival days and the higher 28-day mortality. Therefore, there is an urgent need to explore a safe, effective therapy for recovery of PCs in sepsis patients with thrombocytopenia, especially severe thrombocytopenia.

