### Study design and setting

The study is designed as a randomized, open-label, multi-center, controlled study in 5 tertiary academic medical centers which are medical, surgical or general ICUs. [name]. W (Shanghai General Hospital, China) will coordinate all the operational processes and [name]. Y (Shanghai Jiao Tong University School of Medicine, China) will conduct all the statistical analyses. Eligible patients who give their consent to participate in the study will be randomly assigned in a 1:1 ratio to treat with rhTPO (rhTPO group) or without any platelet-elevating drugs (control group). Both two groups receive appropriate medical treatment according to the current guideline of Surviving Sepsis Campaign (SSC) [6], and will be assessed for the outcomes at baseline, after the intervention and at 28-day follow-up. The end of the study is defined by the last follow-up of the last enrolled patient.

Patients in rhTPO group will be treated with rhTPO (TPIAO™, Shenyang Sunshine Pharmaceutical Co., Ltd. Shengyang, China) at a dose of 15000u/d, subcutaneous injection, for 7 consecutive days. RhTPO in the study is for free. The time from randomization to administration of rhTPO will be within 24 h. The drug will be terminated when PCs reach the standard of clinical recovery of platelets (PCs ≥100 × 10^9^/L or the increasing of PCs ≥ 50 × 10^9^/L lasting for at least 3 days) or severe adverse effects happened. The clinical recovery time of platelets was defined as the time it takes to reach clinical recovery. Patients in control group will not be treated with any platelet-elevating drugs.

In both control and rhTPO groups, there is the same standard of platelet transfusion: when PCs are below 10 × 10^9^/L in the absence of apparent bleeding; or below 20 × 10^9^/L if the patient has a significant risk of bleeding; or below 50 × 10^9^/L if the patient has active bleeding or need invasive operation. During the study, any other platelet-elevating drugs will be forbidden.

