### Study population/ participants

A principle investigator (PI), assisted by a well-trained Co-PI in each clinical center, is responsible for selecting eligible patients based on the eligibility criteria and authorizing the staff to have the patients’ consents. Patients are eligible to be enrolled the study based on the following inclusion and exclusion criteria. Inclusion criteria: 1) age ≥ 18 years, and ≤ 75 years, no limitation of gender; 2) Diagnosis or clinical diagnosis of infection; 3) The change of Sequential Organ Failure Assessment (ΔSOFA) ≥ 2; 4) Platelets counts (PCs) < 50 × 10^9^/L; 5) Informed consent. Exclusion criteria: 1) History of the treatments with chemotherapeutic drugs or heparin drugs within six months; 2) History of bone marrow stem cell disorders, malignancy, or immunologic diseases; 3) History of bone marrow, lung, liver, kidney, pancreas, or small bowel transplantation; 4) Confirmed End-stage renal failure (GFR<10 ml/min, Scr>707 μmol/L); 5) Confirmed Disseminated Intravascular Coagulation (DIC); 6) Confirmed Hemorrhagic brain injury or need craniocerebral operation; 7) Died anticipated within 24 h; 8) Pregnant or lactating patients.

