#### Secondary outcomes

Secondary outcomes of this study have been seen as follow: 1) The changes of platelets counts (PCs) in the first 7 days; 2) The clinical recovery time of PCs; 3) The amount and proportion of blood transfusion (including platelets, RBC, Frozen plasma); 4) The changes of biomarkers of infection including procalcitonin, C-reactive protein (CRP), endotoxin; 5) The changes of the markers of organ function including cardiac, hepatic, renal, coagulation function; 6) The days free from advanced organ support (including vasoactive drugs/mechanical ventilation/renal replacement therapy) at 28 days; 7) The incidence of bleeding event; 8) The incidences of drug-related adverse events; 9) The length of ICU and hospital stay.

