### Data collection

A case report form (CRF) will be used for all patient who met the enrollment criteria to collect the data. Patients will be followed up to 28 days after randomization. The data will be abstracted from the patients’ electronic medical records: age, ethnicity, gender, patients’ type (medical/surgical), co-comorbidities, sites and pathogens of infection. Then, clinical characteristic baseline and laboratory results were tested within the first 24 h after randomization, including markers of organ functions and biomarkers of infection (Procalcitonin, C-reactive protein, Endotoxin). The severity of disease scores will be recorded, including APACHE II, SOFA, and DIC scores [32] in the first 24 h. The basic serum TPO level in patients will be tested by ELISA Kit (R&D Systems, Minneapolis, MN, USA). The clinical data will be tested in the point-in-time followed by protocols on the day of enrollment and periodically thereafter until the time of discharge or death, including the numbers of blood products transfusion (including platelets), antibiotics, concomitant medication, days free from advanced organ support, adverse events and the length of ICU or hospital stay. And if several clinical data or measurements will be performed at one day, the lowest/worst data will be retained. Patient status (survive or death) at the 28 days will be recorded through chart review or contact patients if necessary, and the major causes of death will be recorded if the patients will be died. Flowchart of this study procedure can be seen in Fig. 1.

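### Bleeding is the only haemostatic event named as an outcome; new DIC and thrombosis reach the between-arm safety comparison only indirectly or through unblinded drug attribution

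*Protocol article*

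**What the plan says.** All references are to the protocol article.

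- **Objectives.** The trial asks whether rhTPO is an effective and safe rescue therapy. Fewer bleeding events is one of the hoped-for effects.
- **Background.** DIC is one of four listed mechanisms of low platelets in sepsis: "Sepsis is often accompanied with local microthrombosis or even cause disseminated intravascular coagulation (DIC) to result in massive platelet depletion".
- **Study population/ participants.** Confirmed DIC is an exclusion criterion. No reason is given.
- **Study design and setting.** rhTPO is given by "subcutaneous injection, for 7 consecutive days", and ends sooner on platelet recovery or severe adverse effects. Controls receive no platelet-elevating drug.
- **Blinding.** There is none.
- **Data collection.** "The severity of disease scores will be recorded, including APACHE II, SOFA, and DIC scores [32] in the first 24 h". No later DIC score is stated. Adverse events are among the data collected periodically until discharge or death, and the major causes of death are recorded.
- **Secondary outcomes.** The only haemostatic event is "7) The incidence of bleeding event". Coagulation appears within item 5, "The changes of the markers of organ function including cardiac, hepatic, renal, coagulation function". Item 8 is the incidence of drug-related adverse events. Neither new DIC nor thrombosis is named.

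**The concern.** A drug that raises platelets can bear on haemostasis in two directions. The outcome list names the event that the Objectives expect rhTPO to reduce. It names no event in the other direction, although the Background places microthrombosis and DIC among the causes of thrombocytopenia in this disease.

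The natural place for such an event would be the adverse event outcome, but that is restricted to drug-related events. In the control arm there is no study drug to which an event could be related. In the rhTPO arm the judgement is made by people who know the allocation, and DIC in a septic patient is readily put down to the sepsis. The resulting count does not compare like with like.

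At stake is the word safe in the conclusion. The trial could report bleeding by arm as an event rate and have no matching event rate for clotting.

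**Working it through.** The article has no figure on DIC or thrombosis to reproduce, so the main check sets its sections side by side. A short calculation then shows what the proposed comparison could deliver.

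**Step 1: routes by which new DIC or thrombosis could reach a between-arm result**

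| Route | Section | What it would show | Limit |
|---|---|---|---|
| Bleeding incidence | Secondary outcomes, item 7 | Events by arm | Not clotting; at most a consequence of DIC |
| Coagulation and organ-function markers | item 5 | Change in values | Does not give the number of patients who developed DIC; depends on who is alive to be measured |
| Platelet counts, first 7 days | item 1 | Change in counts | The drug raises them, so consumption may be masked in the treated arm |
| Blood products; days free from organ support | items 3 and 6 | Downstream effects | Not specific to DIC or thrombosis |
| Drug-related adverse events | item 8 | Attributed events | Unblinded attribution; little meaning without study drug |
| Serious adverse event reports | Study design and setting | Drug-associated, unexpected events that are fatal, life-threatening or disabling | Attribution again; a non-life-threatening, non-disabling clot does not qualify |
| All-cause mortality; causes of death | Primary outcomes; Data collection | Fatal cases | Non-fatal cases missed |
| DIC score | Data collection | Status in the first 24 h | No repeat stated |

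No row gives a count of new DIC or thrombosis in both arms free of attribution.

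**Step 2: survival and the markers.** Sample size assumes 28-day mortality of 50% (control) and 30% (rhTPO). With 100 per arm, that leaves 100 × 0.50 = 50 and 100 × 0.70 = 70 patients alive at day 28. The more the arms differ in survival, the less a mean marker change among those still measured can stand in for an event count over all randomised patients.

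**Step 3: precision of the proposed comparison.** The planned number is 100 per arm. The minimum of 91 behind it reproduces with the unpooled formula: (1.96 + 0.8416)² × (0.5×0.5 + 0.3×0.7) / 0.2² = 90.26, rounded up to 91. The point does not depend on this.

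The document gives no event rate, so the rates below are assumptions. The 95% half-width for a difference, with rate p in both arms, is 1.96 × √(2p(1−p)/100). The last column is the two-sided 5% power to detect a doubling of p.

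| Assumed p | Half-width | Power for a doubling |
|---|---|---|
| 5% | ±6.0 points | 27% |
| 10% | ±8.3 points | 51% |
| 20% | ±11.1 points | 88% |
| 30% | ±12.7 points | 99% |

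With no events among 100 patients, the one-sided 95% upper limit is 1 − 0.05^(1/100) = 0.0295, about 3.0%.

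The comparison is therefore a safety estimate. As a test it would be weak unless the events are common.

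**The case against.** The strongest reply is that the plan already has several measures that could go against rhTPO: coagulation and organ-function markers, transfusion, organ-support-free days, adverse events collected to discharge or death, causes of death, and all-cause mortality. Bleeding could itself come out worse on rhTPO. This stands. A reader might infer that DIC after day 1 goes unseen, or that the safety result can only favour the drug; the documents do not support either reading.

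A second reply is that the article condenses a fuller protocol. The flowchart is not shown, the safety parameters reviewed by the monitoring committee are not listed, and a repeat DIC score may be scheduled elsewhere. This stands in part: the absence of a stated later score does not prove that none is planned. It does not answer the outcome list. That list is given in full, numbered, and restricts adverse events to drug-related ones. It is a stated choice, and monitoring by a committee is not a reported between-arm outcome.

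Third, the article gives no reason for excluding DIC, so one cannot say which harm the exclusion was meant to prevent. The Background also reports that TPO decreased platelet aggregation and consumption. Both stand. The point needs no assumption that rhTPO causes DIC or clots, only that a safety claim should be able to show whether they differ by arm.

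Finally, a reader might see a contradiction between excluding DIC at entry and not naming it among the conditions that end treatment. Those rules serve different purposes, and their difference is not an inconsistency.

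**Conclusion.** The point holds in a limited form. Of nine secondary outcomes, one names a haemostatic event, in the direction that rhTPO is expected to improve. None names new DIC or thrombosis. These can enter the comparison indirectly, or through an attribution that is unblinded and has little meaning in the control arm.

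The effect is on the strength of the safety conclusion. The primary outcome, sample size and treatment are untouched. The number of patients concerned cannot be given, because the documents contain no rate for these events; the precision figures rest on assumed rates of 5% to 30%. The conclusion also rests on the article's outcome list being the one that will be followed.

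**What to change.** In Secondary outcomes, add as safety outcomes new thrombotic events and new DIC after randomisation, to day 28. Report them for all patients in both arms regardless of attribution, as differences with confidence intervals, beside bleeding. Keep the drug-related adverse event outcome as a separate listing.

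In Data collection, state that the DIC score used at entry is derived again on those of the 7 treatment days when platelets and coagulation tests are already taken. Show the non-platelet items separately, because the drug raises the platelet item. The article does not name the coagulation tests or their days, so check first that they supply the items of the score.

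Because the arms may differ in survival, say how patients who die without the event are counted. For patients discharged before day 28, the thrombosis question can go with the day-28 status check.

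The cost is one case report form line for thrombosis, a derived score that needs careful reading, and estimates of limited precision with 100 per arm. No change in sample size follows. Thrombotic events should be captured prospectively, since they may not be recoverable later.

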**Fig. 1 Fig1:**
[figure not shown]
Flowchart of RESCUE trial procedure

### Data management and monitor

The data in the study will be managed by clinical trial staffs who will be authorized by the site PI at the sites. The site PI will be responsible for ensuring the accuracy, completeness, legibility, and timeliness of the data reported in the site. Researchers were not permitted to interpret records, and other researchers who are not involved in the patients’ treatment will assess the outcomes. Furthermore, to ensure inter-site reliability, the PIs will explicate operations manual (including the definitions for CRFs and guidelines for collecting data) before data collection and frequent communications among PIs will be kept through e-mail and WeChat during the trial.

Clinical Research Institute of Shanghai Jiao Tong University Medicine School will be responsible for the clinical data management. The Electronic Data Capture (EDC) system will be supplied by Edetek Inc. (Princeton, NJ, USA). All patients’ data will be recorded on paper CRFs and then enter into EDC system. Data in the EDC system will be checked by built-in algorithm, monitored when some modification is required, and traceable to source data. The trial sponsor ([name]. W, Shanghai General Hospital, China) have access to the final trial dataset.

Data and Safety Monitoring Committee (DSMC), independent from the coordinating centers and investigators, will perform an ongoing review of predefined safety parameters and overall study conduct. The DSMC established by Clinical Research Institutes of Shanghai General Hospital and Shanghai Jiao Tong University School of Medicine will be comprised of experts in clinical trials, biostatistics and intensive care medicine.

On all study-specific documents, other than the signed consent, the participant will be referred to by the study code, not by name. All study-specific documents at all centres including source document verification, informed consents, data quality, study drug reconciliation and the table of follow-up will be monitored by DSMC on several occasions during the study, independent from investigators and the sponsor. Besides, the study may also be audited by local or national regulatory authorities.

The study may be terminated or suspended at any time at the following reasons: 1) the request of the study management committee or a regulatory authority; 2) Funding or management problems; 3) Drug-associated severe adverse events. And Clinical Research Institute of Shanghai General Hospital can make the final decision to terminate the trial and will supply reason(s) for the termination or suspension to all the centers. Otherwise, the study is considered terminated upon completion of all patient treatments and evaluations. When discontinuing the trial, all records shall be kept for check.

### Statistical methods

Analyses will be conducted on an intention-to-treat and per-protocol population basis. Data for each assessment will be summarized for each treatment group and the descriptive statistics will be calculated depending on the data distribution for each assessment. Outcomes will be collected at the times defined in the study protocol. The primary efficacy variable will be the change in 28-day mortality. The change in 28-day mortality between the two groups will be analyzed by using Chi-Square. The proportions will be analyzed using logistic regression including baseline as covariate and group as a fixed factor. The comparisons among continuous parametric data were conducted by using t-test or Anova analysis, whereas the A Mann-Whitney U test or a Kruskal-Wallis test were used to analyze continuous nonparametric data. Comparisons between enumeration data ware conducted by Chi-Square or Fisher exact method. Survival comparison between groups was analyzed by using Log-rank analysis. *P* < 0.05 was considered to indicate statistical significance.

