### Sample size

The 28-day all-cause mortality of sepsis patients varies in different patient populations. According to the previous studies, the 28-day mortality of sepsis patients with severe thrombocytopenia was more than 50% [19, 20, 31]. Furthermore, in our single-center, retrospective, cohort study, the 28-day mortality of these patients treated with rhTPO was 29.2%. Our sample size was calculated to detect a 20% difference (rhTPO group 30% Vs Control group 50%) in 28-day mortality. Based on a two-tailed test of two independent means, with a significance (α) level of 0.05 and 80% power, a minimum of 91 patients in each group for a total sample of 182 patients was required. It was assumed that the loss rate of this study is no more than 10%, and the minimum sample of this study was 100 patients in each group for a total sample of 200 patients.

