### Randomization

Eligible patients will be randomly assigned to the control and rhTPO add-on treatment in a dynamic random and competitive design in clinical trial sites. Sequential organ failure assessment (SOFA), Acute Physiology and Chronic Health Evaluation II (APACHE II) scores are as the dynamic equilibrium factors. Randomization will be done after the first assessment, ensuring that the assessing occupational therapist will not be biased at this time by knowing the group assignment. A random number will be generated before the start of this study. The random number list will be kept by the third party and uploaded into a random data assigned system. When a patient is recruited in this study, the patient will then be assigned a random number by the system with corresponding treatment. If a patient is later excluded for any reason, the patient’s position in the randomization list will not be replaced by any new patient. Patients will be recruited consecutively. After forty patients have been recruited, the dynamic arithmetic will be introduced. Then, the random number assigned by the system will based on the equilibrium of dynamic factors.

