### Outcome measures

#### Primary outcomes

Primary outcome of this study is the 28-day all-cause mortality.

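### The test named for 28-day mortality ignores the two scores used to balance allocation; it stays valid and keeps its planned power, but tends to be conservative and forgoes an available gain

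*Protocol article*

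**What the plan says.** All references are to the protocol article.

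- **Primary outcomes:** "Primary outcome of this study is the 28-day all-cause mortality", a yes/no outcome.
- **Statistical methods**, on the test for that outcome: "The change in 28-day mortality between the two groups will be analyzed by using Chi-Square". No covariate or stratifier is mentioned.
- **Statistical methods**, next sentence: "The proportions will be analyzed using logistic regression including baseline as covariate and group as a fixed factor". It does not say whether 28-day mortality is among these proportions, whether the model is primary or supportive, or what the baseline covariate is.
- **Randomization:** "Sequential organ failure assessment (SOFA), Acute Physiology and Chronic Health Evaluation II (APACHE II) scores are as the dynamic equilibrium factors". Also: "After forty patients have been recruited, the dynamic arithmetic will be introduced". With 200 patients planned, about 160 are therefore allocated with regard to these scores.
- **Sample size:** "Our sample size was calculated to detect a 20% difference (rhTPO group 30% Vs Control group 50%) in 28-day mortality". The target is an unadjusted difference of 20 percentage points, with two-sided alpha 0.05, 80% power, 91 per group, and 100 per group after allowing for loss.

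**The concern.** When allocation is steered towards balance on factors that predict the outcome, the arms differ less by chance than under simple randomisation. The chi-square variance does not know this and still counts the variation that the design has removed. The test then rejects a true null hypothesis less often than 5%. Separately, leaving out prognostic covariates costs power in a logistic setting under any allocation method.

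Picking SOFA and APACHE II as balancing factors makes sense only if they are expected to predict death. The design thus relies on their prognostic value and the named primary test does not use it. The next sentence does not settle the matter. Mortality has no baseline value of its own, so the covariate could mean nothing for this outcome, or it could mean baseline characteristics in general. As written, two methods could apply to 28-day mortality and the article does not say how they relate. In an open-label trial it is better to have that choice fixed in advance.

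**Working it through.** **Step 1: the plan's own sample size.** Inputs from Sample size: 50% vs 30%, two-sided alpha 0.05, power 80%. Although the text refers to a test of means, the figure reproduces as a comparison of two proportions with unpooled variance:

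n = (1.960 + 0.842)² × (0.5×0.5 + 0.3×0.7) / 0.20² = 7.849 × 0.46 / 0.04 = 90.3, so 91 per group.

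The pooled-variance formula gives 93. Power of the unadjusted test with pooled null variance is Φ[(0.20√n − 1.960√(2×0.4×0.6)) / √0.46], which is 79.1% at 91 per group and 82.8% at 100 per group. The stated N is thus right for an unadjusted comparison.

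**Step 2: simulation of the allocation.** There were 6,000 trials per scenario. The first 40 patients were allocated by simple randomisation, then by minimisation on SOFA and APACHE II. Control mortality was 50%, with 50% (null) or 30% in the rhTPO arm. The Pearson chi-square was compared with a logistic regression on group and both scores. The article gives none of the following, so they are assumptions: tertile categories, biased coin 0.8, score correlation 0.6, equal log-odds effect of each score, and the AUC of the two scores together. The Monte Carlo standard error is about 0.3 point for type I error and 0.5 point for power.

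| AUC (assumed) | N | Type I, chi-square | Type I, adjusted | Power, chi-square | Power, adjusted | Gain (points) |
|---|---|---|---|---|---|---|
| 0.50 (not prognostic) | 182 | 4.3% | 4.8% | 79.5% | 79.4% | none |
| 0.64 | 182 | 4.0% | 4.9% | 79.5% | 81.5% | 2.0 |
| 0.72 | 182 | 3.4% | 5.1% | 80.7% | 84.7% | 4.0 |
| 0.80 | 182 | 2.4% | 4.9% | 83.0% | 90.0% | 7.0 |
| 0.50 (not prognostic) | 200 | 5.0% | 4.5% | 83.4% | 83.0% | none |
| 0.64 | 200 | 4.9% | 4.8% | 83.7% | 85.1% | 1.4 |
| 0.72 | 200 | 4.0% | 4.8% | 84.9% | 88.4% | 3.5 |
| 0.80 | 200 | 2.9% | 5.1% | 86.6% | 93.0% | 6.4 |

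**Step 3: is the allocation the cause?** With simple randomisation throughout at N=182, the chi-square type I error was 4.6% to 5.2% across the same AUCs. The fall towards 2.4% therefore comes from balancing on prognostic scores and then ignoring them.

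**Step 4: how much is discreteness?** Exact enumeration of the Pearson chi-square with 50% mortality in both equal arms gives a size of 4.45% at 90 per arm, 4.5% at 91 and 5.6% at 100. About half a point of the shortfall from 5% at N=182 is thus a property of the test at that sample size. Measured against the non-prognostic rows, the drop due to balancing is:

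- N=182: 4.3 − 4.0 = 0.3, 4.3 − 3.4 = 0.9 and 4.3 − 2.4 = 1.9 points.
- N=200: 5.0 − 4.9 = 0.1, 5.0 − 4.0 = 1.0 and 5.0 − 2.9 = 2.1 points.

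**Step 5: sensitivity.** A separate simulation with score correlation 0.5, for weaker and stronger scores, gave chi-square type I error of 3.4% and 3.0% at N=182, and 5.3% and 3.6% at N=200. The adjusted analysis had 4.7% to 5.8%, and its power gain was about 2 to 5 points. With weak scores at N=200 the conservatism was not visible.

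**The case against.** **The trial loses no planned power.** A reader might infer that the chi-square leaves the trial underpowered. The documents do not support this: N was set for an unadjusted comparison, and the chi-square delivers 79.5% to 83.0% at N=182 and 83.7% to 86.6% at N=200 in the prognostic scenarios. What is forgone is an optional gain. This stands.

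**The test is not invalid.** Conservatism does not inflate the false-positive rate, so it cannot by itself produce a spurious claim of benefit. This stands.

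**The prognostic strength is assumed.** The article gives no AUC, no coin probability and no score categories, and the first forty patients fall outside the dynamic scheme. This stands: the direction is firm, provided that the scores predict death, but the size is not.

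**An adjusted model is already planned.** A reader might infer the opposite, that no adjustment is foreseen at all. That is also too strong. Mortality is a proportion, the covariate may mean baseline characteristics, and Data collection records both scores. Naming covariates can fairly be left to an analysis plan. But the article does not leave the primary test open: it names the chi-square for 28-day mortality and does not link the regression to it. The mismatch between that stated choice and the stated allocation remains.

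**Adjustment could be carried too far.** An odds ratio alone would not match the risk difference used for sizing, and two covariates could destabilise models for rarer secondary events. Both stand and shape the fix.

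**Conclusion.** The point holds as one of efficiency and clarity that should be changed, not as a threat to validity. The stated primary test does not match the stated allocation, and the one adjusted model mentioned is too loosely worded to close the gap. If SOFA and APACHE II predict death with a joint AUC of about 0.64 to 0.80, the chi-square has a type I error of about 2.4% to 4.0% at N=182 and about 3% to 5% at N=200, part of the shortfall at the smaller N being discreteness. It forgoes roughly 1 to 7 points of power. If the scores are not prognostic, neither effect appears beyond simulation error. These sizes rest on the assumed AUCs, score correlation, tertiles and biased coin.

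**What to change.** Name one primary analysis, in all randomised patients: a logistic regression of 28-day death on group plus SOFA and APACHE II as continuous covariates. Use the values entered in the randomisation system. Data collection dates baseline laboratory results to the first 24 h after randomisation, and rhTPO may start in that same window, so later values could postdate treatment.

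Report the standardised risk difference with 95% CI, that is, the average over all patients of the predicted risk under rhTPO minus the predicted risk under control. This matches the 20-point difference on which the trial is sized. Give the adjusted odds ratio alongside, and keep the chi-square as a supportive unadjusted result. Define the baseline covariate in the logistic regression sentence and say which outcomes it covers. Do not require the same two covariates for secondary proportions with few events.

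The cost is one paragraph in the protocol or analysis plan. Both scores are already needed for allocation, so no extra data or patients are required.
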